#### On-Site and Ongoing Supervision

Experienced CBO staff serve as trainers and provide continuous mentorship to peer volunteers throughout the intervention phase. These trainers, together with CDC supervisors, monitor intervention implementation through regular check-ins, feedback sessions, and review of anonymized communication logs when needed.

### Capacity Building for Project Volunteers

To enhance the understanding of the student MSM volunteers on the project rationale and improve their capacity to implement interventions, a structured training program will be provided prior to project initiation. This training will include both theoretical and practical components, such as (1) lectures to be delivered by experts and CBO trainers on HIV prevention strategies (eg, PrEP and PEP), online counseling skills, and psychological communication techniques; (2) practical simulation exercises focusing on real-world scenarios and case discussions; (3) orientation sessions explaining project-specific tasks, performance assessment indicators, and operational guidelines.

### Intervention Implementation

#### Overview

Trained student volunteers will deliver the intervention package to participants via Enterprise WeChat (a secure communication platform). The package will consist of four key components: structured health education modules, proactive counseling services, PEP assistance, and HIV prevention supply distribution.

#### Structured Health Education Modules

Monthly educational content will be disseminated, featuring curated articles from authoritative HIV prevention platforms operated by CBOs or national organizations (eg, China CDC official accounts). Each module focuses on a specific theme; content development will prioritize cultural relevance and adolescent-friendly design, utilizing infographic-style visual prescriptions tailored to student MSM cognitive preferences.

Educational content will adhere to national guidelines, including Guidelines for HIV Prevention among MSM [23] and Guidelines for Internet-based HIV Interventions [24]. Core content areas will include (1) HIV/STI transmission risks and condom-compatible lubricant usage; (2) PEP/PrEP knowledge and access pathways (eg, initiation within 72 h for PEP); (3) geolocation-enabled testing site information and MSM-specific epidemiological updates; and (4) risks associated with the use of addictive sexual enhancement products.

#### Proactive Counseling Services

Each participant receives biweekly proactive one-on-one counseling conducted by peer volunteers using motivational-interviewing techniques to reinforce safer sexual behaviors and strengthen adherence to preventive measures. These online sessions typically last 10 to 15 minutes and are delivered through WeChat. Core topics include HIV risk-reduction planning, emotional well-being, stigma coping, and linkage to HIV testing or care services.

In addition, a 24/7 online crisis-support channel is available for participants experiencing psychological distress, substance-use crises, or urgent HIV-related concerns. Volunteers are trained to provide first-line counseling and escalate complex cases to CDC supervisors or professional counselors within 24 h.

#### PEP Assistance

For participants reporting high-risk exposures (eg, condomless anal intercourse or needle-sharing), volunteers will provide the following:

Rapid linkage to PEP services: Same-day appointment coordination with PEP-prescribing outpatient clinics using a geolocation database.

Financial assistance: A one-time subsidy of RMB 500 (US $70.88) will be provided upon verified PEP completion (submission of clinic-issued proof). All PEP referrals are monitored through CDC-verified reporting channels to ensure timely initiation and adherence support. Participants with repeated high-risk exposures were assessed for PrEP eligibility in accordance with the Expert Consensus on HIV PrEP in China [25].

#### HIV Prevention Supply Distribution

Participants will receive a discreetly packaged prevention kit via third-party logistics, ensuring privacy protection. The kit will include condoms, water-based lubricants, and STI self-testing kits.

Participants will receive a discreetly packaged prevention kit via third-party logistics, ensuring privacy protection. The kit will include condoms, water-based lubricants, and STI self-testing kits.

Distribution will be limited to a one-time delivery per participant to optimize resource allocation.

Volunteers track delivery confirmation through the digital management platform.

### Study End Points

The study has three predefined endpoints:

HIV seroconversion: Participants with a reactive HIV test result will receive posttest counseling and referral to the local CDC for confirmatory laboratory testing. If HIV infection is laboratory-confirmed, the participant will be withdrawn from further study follow-up and intervention activities.Loss to follow-up: Participants will be considered lost to follow-up if they fail to complete follow-up assessments and cannot be contacted despite repeated attempts.Study completion: Participants who complete the 12-month follow-up period and final HIV/STI testing will be considered as having completed the study.

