## Methods

### Ethical Considerations

Participation in this study will be entirely voluntary, and comprehensive measures will be implemented to ensure participant anonymity and data confidentiality. The study protocol has been reviewed and approved by the Ethics Committee of the Chengdu CDC (Approval No. 2024021).

All participants were required to carefully read the electronic informed consent form prior to enrollment, which will provide detailed information about the study purpose, procedures, potential risks, and benefits. Only those who voluntarily select the “Agree” option will be permitted to proceed with the questionnaire, thereby documenting their informed consent. Participants will have the right to withdraw from the study at any time without any negative consequences.

To prevent coercion or power imbalance between peers, volunteers, and participants were matched across different universities; all volunteers must sign a confidentiality agreement; all participation is anonymous and voluntary. We also conducted dedicated confidentiality training during the pre-project orientation.

To support HIV prevention efforts, the study will provide access to evidence-based online health education, individualized counseling services, and free prevention supplies, including condoms, lubricants, and HIV/STI self-testing kits. Additionally, participants will receive modest financial compensation for completing each survey, in recognition of their time and contribution. Participants received RMB 20 (US $2.83) at baseline, RMB 20 (US $2.83) at the 6-month follow-up, and RMB 20 (US $2.83) at the final 12-month follow-up.

Potential risks primarily will involve the possible inadvertent disclosure of sensitive information related to sexual behavior. However, robust data security and privacy protection protocols will be established, including data encryption, pseudonymization of identifiers, and restricted access to sensitive information, to minimize this risk.

The anticipated benefits of participation—including increased HIV-related knowledge, improved access to prevention services, and facilitation of early detection and timely linkage to care—are expected to outweigh the minimal risks involved.

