#### Sample Size

To estimate the required sample size for a prevalent cohort under an exponential distribution assumption, we adopted the 2-sample Poisson rate comparison framework described by Shiue and Bain [15]. Detailed formulas and derivations are provided in Multimedia Appendix 1.

We assumed a baseline HIV incidence of 4 per 100 person-years (estimated from multiple MSM cohort studies in China [16-18]) and an expected postintervention incidence of 1 per 100 person-years (a 75% relative reduction), with a 2-sided α of .05, 80% power, and an anticipated 10% attrition over 12 months. Based on these assumptions, the required sample size is 484 participants.

The projected reduction to 1 per 100 person-years (75%) was empirically derived. Continuous surveillance of the MSM population in Chengdu observed a 60.9% year-over-year decline in new HIV infections between 2022‐2023 and 2023‐2024 (internal monitoring data available upon request). Building upon this trend, our multilevel intervention—integrating digital education, peer counseling, and PEP subsidies—is expected to produce further improvement. Preexposure prophylaxis (PrEP) combination-prevention intervention internationally has achieved 31.5% relative risk reduction among MSM [19], thus a 75% reduction was adopted as an empirically grounded upper-bound planning scenario.

We anticipated a 12-month retention rate of approximately 90% in this online cohort of student MSM. This assumption is informed by previous longitudinal studies among young men who have sex with men and gay/bisexual men, which have reported 12-month follow-up retention of 85% to 91% under structured follow-up procedures and supportive engagement strategies [20,21]. Given that our study uses multiple retention strategies (scheduled online follow-ups, advance notification of all incentive payments at enrollment, and close coordination through student volunteers), a 10% loss to follow-up was considered an ambitious but achievable design target. Sensitivity analyses at 25%, 50%, and 75% relative reductions and attrition rates of 10% to 20% were prespecified at the fixed N to assess feasibility and robustness (see Multimedia Appendix 2 for summary scenarios).

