### Outcome Measures

#### Primary Outcome

HIV and syphilis incidence rate: The primary outcome is the change in HIV and syphilis incidence rates before and after the intervention, assessed by comparing the postintervention incidence with the baseline incidence among local student MSM populations.

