#### Secondary Outcomes

Secondary outcome measures include (1) changes in sexual behaviors (eg, condom use, number of sexual partners) before and after the intervention; (2) frequency of biomedical intervention utilization (eg, HIV testing, STI testing, PEP, PrEP use); and (3) changes in HIV and STI prevention knowledge and awareness levels.

Detailed definitions of outcome indicators, measurement methods, and data sources are summarized in Table 1.

**Table 1. T1:** Indicators of study outcomes.

Domain	Specific indicator	Definition	Data source
Primary outcomes			
HIV incidence	Comparison between intervention cohort and local student MSM attending university	New HIV cases confirmed by medical institutions per 100 person-years vs surveillance data (2025)	Laboratory reports at 12-month follow-up; CDC^b^ surveillance data
Syphilis incidence	Comparison between intervention cohort and local student MSM attending university	New syphilis cases confirmed by medical institutions per 100 person-years vs surveillance data (2025)	Laboratory reports at 12-month follow-up; CDC surveillance data
Secondary outcomes			
Behavioral Changes			
Risk behaviors	Condom use during anal intercourse Commercial sex engagement Multiple partners	% reporting “always use condoms” in past 3 months % reporting paid sex in past 3 months % with ≥2 sexual partners in past 3 months	Structured questionnaire
Substance use	Psychoactive substance use during sex	% reporting use of chemsex drugs in past 3 months	Structured questionnaire
Testing behaviors	HIV testing frequency STI^c^ screening	% tested for HIV in past 3 months % tested for STIs in past 3 months	Structured questionnaire
Biomedical uptake			
Prevention tools	Condom/lubricant use PrEP^d^/PEP^e^ utilization	% using condom/lubricant % PrEP/PEP initiations	Supply logs; pharmacy data
Attitudinal changes			
Prevention intention	Future condom use intent Testing willingness	% planning to use condoms % willing to undergo future HIV/STI tests	Structured questionnaire
Awareness changes			
Health literacy	PEP/PrEP knowledge HIV/STIs awareness	% correctly describing PEP/PrEP protocols % choosing the right core knowledge about HIV/STIs	Knowledge assessment

a MSM: men who have sex with men.

b CDC: Centers for Disease Control and Prevention.

c STI: sexually transmitted infection.

d PrEP: preexposure prophylaxis.

e PEP: postexposure prophylaxis.

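### Withdrawing confirmed HIV seroconverters from all follow-up makes loss from the co-primary syphilis outcome and the behavioural outcomes depend on HIV; the likely bias is small and avoidable

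*Protocol article*

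**What the plan says.** Study End Points lists HIV seroconversion, loss to follow-up and study completion as three ways in which participation ends. For confirmed HIV the rule has no exception: "the participant will be withdrawn from further study follow-up and intervention activities". It stops data collection as well as the intervention.

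The Primary Outcome section reads: "The primary outcome is the change in HIV and syphilis incidence rates before and after the intervention". Syphilis therefore has the same standing as HIV. Table 1 gives the source of the cohort's data for both as "Laboratory reports at 12-month follow-up", to be set against surveillance data. Secondary outcomes include "changes in sexual behaviors (eg, condom use, number of sexual partners) before and after the intervention", along with paid sex, chemsex, testing, and PrEP and PEP use.

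The testing Overview and Survey Content and Follow-Up place the combined HIV/HCV/HBsAg/syphilis kit and the questionnaire at baseline, month 6 and month 12. The testing Overview also says that every participant is tested at each follow-up, which does not fit the withdrawal rule. Study Design describes participants as their own controls. Statistical Analysis names chi-square tests and logistic regression, and leaves longitudinal models to be used if needed.

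**The concern.** A man confirmed HIV-positive after the month-6 test has no month-12 syphilis result and no month-12 survey. His loss from one primary outcome is triggered by the other. Both infections are sexually transmitted, and the secondary outcomes measure the behaviour that leads to them, so the loss is unlikely to be independent of what is being measured.

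If seroconverters have more syphilis and more risk behaviour than the rest, removing them lowers the observed syphilis rate and makes month-12 behaviour look safer. Both errors favour the intervention, and there is no concurrent arm in which the same loss would occur. The limitations text at the end of the Discussion says that the study will lean on behavioural outcomes because infections are expected to be rare.

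This is a rule about which data are collected. An analysis plan cannot recover tests and surveys that the protocol tells the team not to obtain.

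**Working it through.** **Inputs from the protocol (Sample Size).** "We assumed a baseline HIV incidence of 4 per 100 person-years"; 1 per 100 person-years expected after the intervention; two-sided alpha 0.05; 80% power; 10% attrition; N = 484.

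**Inputs not in the documents (assumptions).** Syphilis rate in men who do not seroconvert: 3-8 per 100 person-years. Rate ratio in seroconverters: 2-10. A harsher set: 3-5 per 100 in the rest and 20-40 per 100 in seroconverters. Prevalence of a risk behaviour: 30-50% in the rest and 60-100% in seroconverters.

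**1. The plan's own figure.** For two Poisson rates with equal person-years, n = (1.960 + 0.842)² × (0.04 + 0.01) / (0.04 − 0.01)² = 436.0. Dividing by 0.90 gives 484.5, which reproduces the stated 484.

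**2. How many men the rule removes by month 6.** 484 × (1 − exp(−rate × 0.5)):

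| HIV rate per 100 PY | Men removed | Share of 484 | Syphilis person-years lost |
|---|---|---|---|
| 1 | 2.4 | 0.5% | 2.4 × 0.5 = 1.2 |
| 4 | 9.6 | 2.0% | 9.6 × 0.5 = 4.8 |

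About as many again seroconvert between months 6 and 12 (2.4 and 9.4). Most of these would be found at the month-12 test and keep their data, apart from any found at an off-schedule test. Planned attrition, for comparison, is 0.10 × 484 ≈ 48.

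**3. Syphilis rate.** Let m be the men removed, r the rate in the rest and s the rate in seroconverters. With everyone kept to month 12 the rate is [(484 − m)r + ms] / 484. With removal at month 6 it is [(484 − m)r + 0.5ms] / (484 − 0.5m).

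| HIV rate | Assumption | Kept | Removed | Relative change |
|---|---|---|---|---|
| 1 | r = 5, ratio 2 | 5.025 | 5.012 | −0.25% |
| 1 | r = 5, ratio 10 | 5.224 | 5.112 | −2.1% |
| 4 | r = 5, ratio 2 | 5.099 | 5.050 | −1.0% |
| 4 | r = 5, ratio 10 | 5.891 | 5.450 | −7.5% |
| 4 (m = 10) | r = 5, s = 20 | 5.310 | 5.157 | −2.9% |
| 4 (m = 10) | r = 3, s = 40 | 3.764 | 3.386 | −10.1% |

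At an HIV rate of 1 per 100, the harshest pair (r = 3, s = 40) gives −2.4% with m = 2 and −2.9% with m = 2.4.

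The largest absolute gap with r from 3 to 8 and a ratio up to 10 is at r = 8: 9.43 − 8.72 = 0.7 per 100 person-years. With about 460 person-years (midway between 484 and 436), the 95% half-width is 1.96 × √(r/460), or 1.6, 2.0 and 2.6 per 100 for r = 3, 5 and 8.

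**4. Behavioural percentage.** If month 12 is compared with the whole baseline sample, the shift with no behaviour change is share removed × (prevalence in seroconverters − prevalence in the rest).
- At 1 per 100: 0.5% × 10 to 70 points = 0.05 to 0.35 points.
- At 4 per 100: 1.98% × 10 to 70 points = 0.2 to 1.4 points.

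The 95% half-width for a percentage of 30-50% at n = 436 is 4.3 to 4.7 points.

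**5. A literal reading of Table 1.** If only month-12 reports count, men confirmed at month 6 leave the syphilis outcome entirely. With r = 5, the rate falls from 5.10 to 5.00 (−2%) at an HIV rate of 1 and ratio 5, and from 5.89 to 5.00 (−15%) at an HIV rate of 4 and ratio 10.

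**The case against.** The strongest reply is that few men and few data are involved. HIV and syphilis are read from one kit and the survey is given at the same time points, so a man first reactive at month 12 still has a syphilis result and can complete that survey. A man reactive at month 6 has given syphilis data up to then. Ten removals also presuppose that the intervention has no effect on HIV; at the planned rate it is about two. The higher risk in seroconverters is assumed. All of this stands, and it limits the size of the point.

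A second reply is that Study Design implies a paired comparison, which drops removed men from both time points. That removes the shift in step 4, though the men analysed are still a selected group. The article does not say that month 12 will be compared with the full baseline; the tests named in Statistical Analysis only leave this open.

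A third reply is that the cohort is defined as HIV-negative, so ending follow-up at seroconversion is natural. That holds for HIV incidence but not for syphilis or behaviour.

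A reader might also infer that the rule contradicts the promised linkage to care ("facilitation of early detection and timely linkage to care" and "Core topics include HIV risk-reduction planning, emotional well-being, stigma coping, and linkage to HIV testing or care services"). The documents do not support this. Study End Points provides counselling and referral before withdrawal, the testing Overview requires immediate referral after a positive test, and Comprehensive Risk Documentation has volunteers follow referred men until confirmatory results are recorded. Proactive Counseling Services makes no promise about the period after withdrawal.

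**Conclusion.** The point holds in a limited form. The rule makes loss from the syphilis and behavioural outcomes depend on HIV seroconversion for men confirmed before month 12, about 0.5% to 2% of the cohort.

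The direction, toward apparent improvement, rests on the assumption that these men carry more risk. Under the assumed rates, the understatement of syphilis incidence is roughly 0.25-2% at 1 per 100 person-years (just under 3% at the harshest pairing) and 1-10% at 4 per 100. The literal reading of Table 1 raises the top of the range to about 15%. The behavioural shift is at most about 1.4 points, and only in an unpaired comparison. Each of these lies within the sampling error shown above.

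A reader might infer that every seroconverter disappears from both outcomes, or that the rule alone could make the cohort look improved. Neither follows: month-12 seroconverters contribute, the effect is too small to produce a visible improvement, and HIV incidence is unaffected because the event is counted before withdrawal. Severity is minor to moderate; the reason to act is that the loss is outcome-dependent, built in by rule and cheap to avoid.

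**What to change.** In Study End Points, make confirmed HIV the end of follow-up for the HIV outcome only. Keep consenting seroconverters in the scheduled syphilis/STI testing and in the remaining surveys, and count their syphilis person-time to month 12. Align the testing Overview with this, and state in Table 1 that confirmed syphilis found at month 6 counts.

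Base the behavioural before-after comparison on men observed at both time points, and report the baseline values of any seroconverters who do withdraw. Because behaviour after a diagnosis partly reflects the diagnosis, add a sensitivity analysis that excludes post-diagnosis data. Which intervention activities continue after diagnosis is for the investigators to decide; this change concerns data collection only.

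The cost is revised protocol and consent wording, about 2 to 10 further surveys and syphilis test results, and RMB 20 per completed survey. Enrolment is reported as ongoing, so the change is most useful if made before month-6 results start to remove men.

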### Outcome Measures

#### Primary Outcome

HIV and syphilis incidence rate: The primary outcome is the change in HIV and syphilis incidence rates before and after the intervention, assessed by comparing the postintervention incidence with the baseline incidence among local student MSM populations.

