**Methods:**

This prospective before-and-after self-controlled cohort study will evaluate the effectiveness of a 12-month internet-based intervention targeting university student MSM in Chengdu. A total of 484 HIV-negative student MSM among the MSM population will be recruited through WeChat and Blued. Trained student volunteers, supervised by community-based organization staff, will deliver monthly health education, one-on-one counseling, postexposure prophylaxis navigation, and HIV or sexually transmitted infection (STI) self-testing kits via secure online platforms. Participants will complete behavioral surveys and HIV/syphilis/hepatitis C virus/hepatitis B surface antigen self-tests at baseline, 6 months, and 12 months. Primary outcomes included changes in HIV and syphilis incidence rates; secondary outcomes included changes in sexual behaviors, HIV/STI testing frequency, preexposure prophylaxis/postexposure prophylaxis uptake, and knowledge improvement.

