### Statistical Analysis

Upon completion of data collection, all survey data will be exported from the Wenjuanxing platform for data cleaning and preprocessing to ensure accuracy, completeness, and consistency. Data management and analysis will be conducted using established statistical software packages, including SPSS, Stata, or R.

Descriptive statistics will be used to summarize participant characteristics and key study variables. Categorical variables will be presented as frequencies and percentages, while continuous variables will be reported as means with SD or medians with IQR, depending on data distribution. The normality of continuous variables will be assessed using Shapiro-Wilk tests and visual inspection of histograms/Q–Q plots. Univariate analyses, such as chi-square tests for categorical variables and *t* tests or nonparametric tests for continuous variables, will be used to assess preliminary associations between independent variables and outcome measures. Multivariate analysis will be performed using logistic regression models (for binary outcomes) to identify factors independently associated with key study end points, adjusting for potential confounders. If advanced statistical modeling (eg, Cox proportional hazards models, generalized estimating equations) is deemed necessary to address specific research questions or to handle longitudinal data, additional statistical expertise will be sought to ensure appropriate application and interpretation of these methods. A 2-sided *P* value <.05 will be considered statistically significant.

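### HIV and syphilis incidence are both primary, but the stated 5% error and 80% power describe the HIV test alone, and the article does not say which result decides

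*Protocol article*

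**What the plan says.** The primary outcome is described in three places:

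- **Abstract, Methods.** Plural: "Primary outcomes included changes in HIV and syphilis incidence rates".
- **Primary Outcome section.** Singular, with the two infections joined: "The primary outcome is the change in HIV and syphilis incidence rates before and after the intervention".
- **Table 1.** Separate primary rows for HIV and syphilis, each with its own comparison of confirmed new cases per 100 person-years in the cohort against 2025 surveillance data.

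The only significance threshold in the Statistical Analysis section is general and not tied to any endpoint: "A 2-sided *P* value <.05 will be considered statistically significant".

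The Sample Size section concerns HIV only. It says "we adopted the 2-sample Poisson rate comparison framework" and "We assumed a baseline HIV incidence of 4 per 100 person-years", with 1 per 100 person-years expected after the intervention, "with a 2-sided α of .05, 80% power, and an anticipated 10% attrition over 12 months". The result is 484 participants. The article gives no syphilis rate, expected effect or power, and it does not say whether HIV, syphilis, either or both must be significant for the primary objective to be met.

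**The concern.** Two outcomes carry primary status, one was sized, and that one received the whole 5%. Three decision rules fit the text: HIV alone decides, both must be significant, or either suffices. They differ in false-positive rate and in power, and only the first matches the Sample Size section.

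A split result is realistic. The protocol calls its 75% reduction an upper-bound planning scenario and concedes in its limitations that the reduction may be optimistic and that incident infections will be rare. At the smaller reductions it lists for sensitivity analysis, HIV power is low (see the working). A non-significant HIV result beside a nominally significant syphilis result, or the reverse, could then be reported as success on a primary outcome. Nothing in the article prevents this, and readers would take the 5% and 80% to apply to that claim when they do not.

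**Working it through.** **Inputs.** From Sample Size: HIV rates 0.04 and 0.01 per person-year, two-sided alpha .05, 80% power, 10% attrition, two-sample Poisson comparison. From Statistical Analysis: two-sided .05 for every test. The correlation between the HIV and syphilis test statistics is not given, so a range is shown.

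**1. The plan's own figure.** With an unpooled normal approximation and equal person-time in the two samples:

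n = (1.960 + 0.842)² × (0.04 + 0.01) / (0.04 − 0.01)² = 436.05

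436.05 / 0.90 = 484.5, which agrees with the stated 484. The same formula at two-sided .025 gives 528.06 / 0.90 = 586.7. The 484 therefore spends the full two-sided .05 on HIV and leaves nothing for a second primary test.

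**2. Error if either infection suffices, both null hypotheses true.** Under independence: 1 − 0.95² = 0.0975. The upper bound for any correlation is .05 + .05 = .10. From the bivariate normal distribution with critical value 1.96:

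| Correlation | Either significant (two-sided) | Either significant, direction of benefit | Both significant |
|---|---|---|---|
| 0 | 9.75% | 4.94% | 0.25% |
| 0.3 | 9.51% | 4.76% | 0.49% |
| 0.5 | 9.07% | 4.54% | 0.93% |
| 0.8 | 7.81% | 3.90% | 2.19% |
| 0.95 | 6.46% | 3.23% | 3.54% |

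The benefit column should be compared with 2.5% for a single two-sided .05 test.

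**3. Error under the other two rules.** If HIV alone decides, it is 5%. If both are required, it is at most 5%, because a false claim needs at least one true null hypothesis to be rejected at .05. It takes the values in the last column when both nulls are true.

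**4. Power.** HIV power with 436 person-years per sample is Φ(0.03 / √(0.05/436) − z).

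- At .05: Φ(2.801 − 1.960) = 80.0%.
- At .025: Φ(2.801 − 2.241) = 71.2%.
- At .05 with a 50% reduction (0.04 vs 0.02): Φ(0.02 / √(0.06/436) − 1.960) = about 40%.
- At .05 with a 25% reduction (0.04 vs 0.03): Φ(0.01 / √(0.07/436) − 1.960) = about 12%.

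If both must be significant, joint power cannot exceed the smaller of the two powers. It is therefore at most 80% under the planning assumptions, and it cannot be put more exactly without a syphilis rate and effect.

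**5. Sensitivity to the choice of test.** The article names no test for the incidence comparison. Assume 436 person-years per sample, both infections at 4 per 100 person-years (for syphilis, an assumption) and independence. A score test then has size 5.03% per infection and 9.80% for either. An exact conditional test is conservative at these counts, at 3.26% and 6.42%. Either way, the rate for either infection is almost twice that for one.

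**The case against.** A reader might infer that the trial's chance of a false primary result is 9–10%. The documents do not support that. No sentence says that either infection suffices. The Primary Outcome section joins the two, and the Sample Size section points to HIV. Under either of those rules the error is at most 5%. Even under an either rule, 9–10% needs independence or moderate correlation. Both infections are sexually acquired and measured in the same men, so positive correlation is plausible. The figure also counts false findings of harm; in the direction of benefit it is about 4.9%. All of this stands, and the figure must be given as conditional.

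Other points also stand in part. That each infection is tested at .05 is inferred from a general sentence, although no other threshold appears. The power figures use the equal-sample framework of the Sample Size section, whereas Table 1 compares the cohort with surveillance data whose person-time is not given. A multiplicity procedure may sit in an analysis plan that is not shown, and the article's appendices on sample size were not seen either. The limitations paragraph promises cautious interpretation of incidence changes and reliance on behavioural outcomes.

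These points narrow the concern but do not remove it. Which outcome is primary, and which one the sample size serves, is protocol content. The article addresses both, and the two do not match. A later multiplicity procedure would not change what the outcome and sample-size sections tell readers, and a promise of caution is not a decision rule.

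**Conclusion.** The point holds in a conditional form. The article lists two primary outcomes, applies one unadjusted threshold and sizes for HIV only, so its 5% and 80% describe the HIV test alone. If either infection may carry the primary claim, the two-sided familywise error is up to about 10% (9.75% at correlation 0, 9.1% at 0.5, 7.8% at 0.8), and false benefit is about 4.9% against 2.5%. If both are required, the error is controlled, but the 80% is only a ceiling and the actual power is unknown. If HIV alone decides, both stated figures stand.

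The error figures assume approximately normal test statistics and an unadjusted .05 for each infection. The power figures assume the protocol's HIV rates and 436 person-years in each of two samples. The 484 itself reproduces and is not in question.

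**What to change.** In the Primary Outcome section and Table 1, name HIV incidence as the primary test at two-sided .05, which matches the basis of the 484. Test syphilis incidence at two-sided .05 only if HIV is significant (fixed sequence). Otherwise report it as a rate ratio with a 95% confidence interval and no claim of significance. Align the abstract, and state in the Sample Size section that the 80% power refers to HIV only.

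Two alternatives are acceptable if syphilis is to stay fully primary:

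- **Require both to be significant.** Say so, and drop the 80% for the joint claim.
- **Allow either, with Holm's procedure.** The smaller P value is compared with .025 and, if it passes, the larger with .05. HIV power at the .025 step is about 71% under the equal-sample assumptions; restoring 80% there would take about 587 participants.

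The preferred change affects wording only. Enrolment, data collection and the 484 are untouched. Its price is that syphilis alone could no longer support a primary effectiveness claim when HIV is not significant. Enrolment has begun, so the change should be dated and made before outcome data are analysed.
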